## Abstract

**Background:**

In general, human papillomavirus (HPV) vaccines have demonstrated efficacy in young women worldwide, but there is limited evidence on the efficacy of the quadrivalent HPV6/11/16/18 vaccine in adult women and no evidence of its effectiveness in Japanese adult women in particular. This study aims to evaluate the efficacy of the quadrivalent HPV6/11/16/18 vaccine for persistent HPV16/18 infection in Japanese women aged 27–45 years.

**Methods:**

This is an interventional, nonrandomized, non-double-blind prospective cohort study designed to compare the rates of persistent HPV16/18 infection between the vaccinated arm and unvaccinated arm. The subjects will consist of all women aged 27–45 years who have normal cytology results confirmed by cervical cancer screening from May 2019 to March 2021. The follow-up time is two years. The subjects will be divided into two groups: the vaccinated group and the unvaccinated group. The study will need to enroll 600 vaccinated participants (experimental arm) and 2200 unvaccinated participants (control arm).

**Discussion:**

The findings of this trial (HAKUOH study) might provide the first local evidence on the subject and be significantly useful not only to medical academia but also to the Japanese Ministry of Health, Labour and Welfare. The findings could contribute to public health improvement by providing local supportive knowledge on the prevention of HPV infection through HPV vaccination in young adult women in Japan, where active recommendations have been suspended for a long time due to adverse effects.

**Trial registration:**

Trial registration number: NCT04022148.

Registration began on December 1, 2019.

## Background

In April 2013, the Ministry of Health, Labour and Welfare (MHLW) started a national vaccination program for women aged 12–16 years in Japan. However, human papillomavirus (HPV) vaccinations were reportedly associated with serious adverse events, and in June 2013, the MHLW announced the suspension of the active recommendation of HPV vaccination. Since then, the vaccination rate in Japan has declined drastically from approximately 70% in 2013 to 1% in 2018 [1].

The very low vaccination rate in Japan has attracted great attention among different institutions. The Japanese Society of Obstetrics and Gynecology, Japanese Society of Gynecologic Oncology, and Japanese Association of Obstetricians and Gynecologists have advised the MHLW to re-implement their strong recommendation for HPV vaccination. The Global Advisory Committee on Vaccine Safety also stated no reason to suspend HPV vaccination or its active recommendation. However, their advice has not led to the MHLW reversing their decision to suspend the active recommendation [2, 3], and a longer time is expected before a strong recommendation is made again.

A previous study showed that the HPV infection rate will increase for every 1-year delay in resuming the active recommendation [4]. This finding suggests that the age of the high-infection-rate group will also increase. Globally, there is limited evidence on the effectiveness of the HPV vaccine in adult women [5, 6], and to our knowledge, there are no available data on the effectiveness of the vaccine in Japanese adult women. Therefore, data on the effectiveness of the vaccine in Japanese adult women will be very valuable and are urgently needed for the catch-up program for these women, as they were not vaccinated for HPV after the active recommendation for vaccination was suspended.

Adult women are not covered under the national immunization program of Japan due to cost-effectiveness concerns, which might be attributed to the high prevalence of persistent HPV16/18 infection in this population. In this study, we will focus on women with normal cytology results because we verified that approximately 99% of the women with normal cytology results have HPV16/18 negative results, as described in our previous study (Fukui Cervical Screening [FCCS] study) [7]. This study (the HAKUOH study) therefore aims to evaluate the efficacy of the quadrivalent HPV6/11/16/18 vaccine (Gardasil®) in healthy Japanese young adult women (aged 27–45 years) with normal cytology results on cervical cancer screening.

## Methods

### Study design

This is an interventional, nonrandomized, non-double-blind prospective cohort study that aims to compare the rate of persistent HPV16/18 infection between the vaccinated arm and unvaccinated arm, as shown in Fig. 1.

**Fig. 1 Fig1:**
[figure not shown]
Study design. IC*: IC to participant in the study and to be sent the recommendation for vaccination

### Subjects and vaccine

The subjects will consist of all women aged 27–45 years who have normal cytology results confirmed by cervical cancer screening programs from May 2019 to March 2021. All women will have Japanese nationality and live in the Fukui Prefecture of Japan. In the Japanese cervical cancer screening program, the government covers the cost of cytology tests. Women are screened every 2 years. The uptake rate for cervical cancer screening in Japan is approximately 40%, with no regional differences. The data collection began in December 2019. The follow-up time will be 2 years because in the Japanese cervical cancer screening program, women are screened every 2 years. The inclusion criteria are as follows: normal cytology results confirmed by cervical cancer screening from May 2019 to March 2020, aged 27–45 years, an intact uterus, and willingness to undergo the HPV-DNA test (cobas4800) within 12 months. The exclusion criteria are as follows: pregnancy, treatment or follow-up evaluation for CIN within the previous 12 months, and previous administration of the HPV vaccine. The subjects will complete the questionnaire about sexual behavior and whether or not they were previously tested for HPV. The subjects will be divided into two groups: the vaccinated group and the unvaccinated group. In the experimental arm comprises women who have been vaccinated three times in 1 year after NILM confirmation by cytology. These women will participate in the cervical cancer screening program after 2 years. We will obtain a residual part of the sample for cytology, and the sample will be used for the HPV test. In women with HPV16/18-positive cells, p16 and Ki67 expression will be analyzed to judge persistent infection. The control arm will comprise women who participate only in the cervical cancer screening program after 2 years. We will obtain a residual part of the sample for cytology, and the sample will be used for the HPV test. In women with HPV16/18-positive cells, p16 and Ki67 expression will be analyzed to judge persistent infection. Subjects in 11 hospitals/clinics who consent to be vaccinated will be enrolled in the vaccinated group and will receive the quadrivalent HPV6/11/16/18 vaccine (Gardasil®) at day 1, month 2, and month 6. Subjects who refuse to be vaccinated will be enrolled in the unvaccinated group.

### Efficacy end point and case definition

The primary efficacy end point is the incidence of persistent HPV16/18-related infection over 2 years. The secondary efficacy end point is twofold: the incidence of persistent HPV16/18-related infection over 2 years by age group (27–30/31–35/36–40/41–45 years) and the consent rate for vaccination by age group (27–30/31–35/36–40/41–45 years). Women in both arms will receive routine cytology screening and an HPV-DNA test (cobas® 4800 system; Roche Diagnostics, Mannheim, Germany) 2 years after the first visit. Among women with HPV16/18-positive cells in both groups, p16 and Ki67 expression will be analyzed using the CINtec® PLUS kit (Roche Diagnostics). Persistent infection is defined as cases in which there are HPV16/18-positive cells overexpressing p16 and Ki67 [8].

### Statistical analysis

Data for HPV16/18 infection, cervical lesions and potential confounders (e.g., age, sexual activity status) from all subjects will be included in the analysis. The association among all data will be analyzed. The chi-squared test will be used to compare the incidence of persistent infection between the vaccinated and unvaccinated groups. *P*-values of < 0.05 will be considered statistically significant. All statistical analyses will be carried out using SPSS version 25.

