### Sample size justification

Based on the assumed incidence rate of persistent infection among adult women (0.9 per 100 person-years) and an assumed risk reduction of 80% [8], for a two-sided test of the null hypothesis, the ideal sample size of the vaccinated group is 537 women and that of the unvaccinated group is 1611 women [9]. A power of 80% and a significance level of 0.05 will be set to control for a type I error. We discussed the sample size justification during the research meeting among researchers. Assuming that the dropout rate is 10% in the vaccinated group and 25% in the unvaccinated group, we will need approximately 600 vaccinated women and 2200 unvaccinated women. To enroll 600 vaccinated participants, it will be necessary to obtain informed consent from 700 participants, assuming that 85% of women actually get inoculated after receiving explanations of the vaccine and agreeing to be inoculated. Additionally, to enroll approximately 2200 unvaccinated participants, 2100 women who do not consent for vaccination will be included in the group in addition to the 15% of women mentioned above who will not actually get inoculated. Therefore, the sample size will be approximately 2800 women who are negative for intraepithelial lesions or malignancy.

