
A possible limitation of the study is that the study design involves a nonrandomized, and not randomized, intervention. If the study were to adopt a randomized intervention design, we speculate that the participation of the patients cannot be assured under current circumstances in Japan, where the MHLW has suspended its strong recommendation for HPV vaccination.

The findings of this trial might provide robust local evidence supporting HPV vaccination among young adult women aged 27–45 years who show negative cytology results. By utilizing the data from this study, we intend to develop a platform covering both cervical cancer screening and HPV vaccine recommendations for those proven to have negative cytology results. This new platform might serve as an effective means to drive HPV vaccination among those not covered under the national immunization program of Japan and raise questions about the rigid state of the 5-year national immunization program. This study could provide local supportive evidence for preventing HPV infection through HPV vaccination in young adult women and thus contribute to public health improvement in Japan, where active recommendation of HPV vaccination has been suspended by the MHLW for a long time.

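### The only between-arm comparison named is an unadjusted chi-squared test, although vaccination is self-selected and the listed confounders are not tied to that comparison

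*Protocol article*

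**What the plan says.** All passages are in the Protocol article.

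- **How the arms form.** Study design describes a nonrandomized, open cohort study. Under Subjects and vaccine, "Subjects in 11 hospitals/clinics who consent to be vaccinated will be enrolled in the vaccinated group", and "Subjects who refuse to be vaccinated will be enrolled in the unvaccinated group". Sample size justification adds a second route into the control arm. About 2100 women who decline are to be joined by women who agreed but were not vaccinated: "in addition to the 15% of women mentioned above who will not actually get inoculated".
- **What is collected.** "The subjects will complete the questionnaire about sexual behavior and whether or not they were previously tested for HPV" (Subjects and vaccine). Age is known from eligibility.
- **What is analysed.** Statistical analysis says that data on "potential confounders (e.g., age, sexual activity status) from all subjects will be included in the analysis", and that associations among all the data will be examined. It then names the comparison of the arms: "The chi-squared test will be used to compare the incidence of persistent infection between the vaccinated and unvaccinated groups", at P < 0.05. It names no regression, stratification, matching or weighting.
- **Related text.** Efficacy end point and case definition lists incidence by four age bands as a secondary end point. The Discussion concedes that "A possible limitation of the study is that the study design involves a nonrandomized, and not randomized, intervention" and names no analytic remedy.

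**The concern.** The stated aim is vaccine efficacy, and the arms are separated by each woman's own decision. That decision plausibly depends on things that also drive exposure to HPV16/18, such as age, sexual behaviour and previous HPV testing. The protocol recognises this by calling age and sexual activity potential confounders and by collecting the data. It then fixes a comparison that cannot use them. The test also gives a P-value and no estimate of efficacy.

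If the text is followed as written, a significant result could partly reflect lower-risk women choosing vaccination. A weak or null result could partly reflect higher-risk women choosing it. The article hopes to inform public-health policy, so this distinction matters to its readers.

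**Working it through.** **Inputs from the Protocol article (Sample size justification)**

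- Control incidence is 0.9 per 100 person-years. Over 2 years this is about 2 x 0.9% = 1.8%.
- Risk reduction is 80%, so vaccinated risk is 0.2 x 1.8% = 0.36%.
- Enrolment is 600 and 2200, with dropout of 10% and 25%. Analysable women: 600 x 0.90 = 540 and 2200 x 0.75 = 1650.
- Expected events: 540 x 0.0036 = 1.9 vaccinated and 1650 x 0.018 = 29.7 unvaccinated.
- Controls: 700 x 15% = 105 consenters not inoculated, plus 2100 who decline, gives 2205, in line with the stated 2200.

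**The plan's own figure.** The plan states 537 and 1611 women for 80% power, two-sided 0.05. A pooled two-proportion formula (1.8% vs 0.36%, 1:3) gives 597 and 1791. At 537/1611, power is 74.5% by normal approximation and 79.1% by exact enumeration of the uncorrected chi-squared test. I do not call the stated size wrong here, and this point does not depend on it. It does look like the size for a crude comparison of two proportions, with no visible allowance for adjustment.

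**Confounding by one binary risk factor.** Let its prevalence be pV in vaccinated and pU in unvaccinated women, and its relative risk RR. The crude risk ratio is the true one multiplied by

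B = [1 + pV(RR - 1)] / [1 + pU(RR - 1)].

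The documents give no values for pV, pU or RR; all are assumptions. Rejection probabilities come from exact enumeration of the uncorrected Pearson test at 540/1650 with control risk 1.8%. Without confounding, the test rejects in 4.9% of trials with no vaccine effect and has 78.5% power for an 80% reduction.

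Lower-risk women choose vaccination, and the vaccine has no effect:

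| pV, pU, RR | B | Apparent reduction | Test rejects |
|---|---|---|---|
| 10%, 30%, 3 | 1.20/1.60 = 0.75 | 25% | 8.6% |
| 5%, 30%, 5 | 1.20/2.20 = 0.545 | 45% | 22.8% |

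Higher-risk women choose vaccination, and the true reduction is 80% (apparent reduction = 1 - 0.2B):

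| pV, pU, RR | B | Apparent reduction | Power |
|---|---|---|---|
| 30%, 10%, 3 | 1.60/1.20 = 1.33 | 73% | 66% |
| 30%, 10%, 5 | 2.20/1.40 = 1.57 | 69% | 57% |

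A milder case, 20% vs 40%, gives B = 1.2/1.4 = 0.857 for RR 2 and 1.4/1.8 = 0.778 for RR 3. A vaccine with no effect then shows a reduction of 14% to 22%.

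**Price of adjusting.** If the covariates explain a share R² of the variance in vaccination status, the size needed grows by about 1/(1 - R²). R² is assumed.

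- R² = 0.05: 597/0.95 gives 629 vaccinated and 1791/0.95 gives 1886 unvaccinated. Power at 537/1611 falls from 74% to 72% (normal approximation).
- R² = 0.20: 597/0.80 gives 747 and 1791/0.80 gives 2239. Power at 537/1611 falls to 62%.

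**The case against.** The strongest counter-argument is the plan's own sentence that confounder data will be included in the analysis. Naming variables as confounders and including them can fairly be read as an intention to adjust. This is a condensed article, and a covariate list or model form is commonly left to the full protocol or analysis plan. A reader might therefore infer that the trial will not adjust at all; the documents do not support that. What stands is narrower: the sentence is not linked to the primary comparison, and the sentence that does define that comparison names a test that cannot use covariates. That is a stated choice, not a missing detail.

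Other points have partial force:

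- The by-age secondary end point lets confounding by age be inspected. It is not an age-adjusted primary estimate and does nothing for sexual behaviour.
- The Discussion is open about nonrandomization, though it offers no remedy.
- The illustrations rest on chosen inputs. The 23% rejection rate needs a six-fold imbalance together with a relative risk of 5. The milder null case in the table gives 8.6%.
- Adjustment is not free. With about 2 vaccinated events, any adjusted estimate is fragile. A propensity score eases model fitting but adds no outcome information.

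**Conclusion.** The point holds in limited form. Vaccination is self-selected, confounders are recognised and collected, and the only comparison of the arms that is named is unadjusted. Followed as written, it gives a potentially confounded answer to an efficacy question.

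Direction and size are unknown. Under the assumptions tabulated above, the distortion runs from a spurious 25% to 45% reduction (rejection in 9% to 23% of trials) to a true 80% reduction appearing as 73% to 69%. These are illustrations, not forecasts. It would go too far to conclude that the bias favours the vaccine, since nothing in the documents settles its direction. It would also go too far to call the crude result worthless: if the true reduction is as large as the design assumes, even the adverse cases shown leave most of it visible. Nor are the controls simply refusers, because about 105 of some 2200 are consenters who were not inoculated.

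**What to change.** In Statistical analysis, make the primary comparison a pre-specified, confounder-adjusted one. Name the covariates from those already collected: age, the sexual-behaviour items and previous HPV testing.

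Choose a method suited to about 2 vaccinated and 30 unvaccinated events. Propensity-score weighting or stratification would serve, as would a penalised model with few covariates. An ordinary multivariable logistic model with many terms would be too sparse. If weighting is used, state the target population, because some weights (overlap weights, for instance) change it.

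Report an adjusted risk ratio or risk difference with a 95% confidence interval by a method suited to sparse data. Keep the chi-squared test as descriptive.

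No new data collection is needed for these covariates. The cost is some precision: power of roughly 72% to 62% instead of 74% at 537/1611 by normal approximation, if the covariates explain an assumed 5% to 20% of vaccination status. The sample size text should acknowledge this. Unmeasured confounding would remain and should still be listed as a limitation.

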### Sample size justification

Based on the assumed incidence rate of persistent infection among adult women (0.9 per 100 person-years) and an assumed risk reduction of 80% [8], for a two-sided test of the null hypothesis, the ideal sample size of the vaccinated group is 537 women and that of the unvaccinated group is 1611 women [9]. A power of 80% and a significance level of 0.05 will be set to control for a type I error. We discussed the sample size justification during the research meeting among researchers. Assuming that the dropout rate is 10% in the vaccinated group and 25% in the unvaccinated group, we will need approximately 600 vaccinated women and 2200 unvaccinated women. To enroll 600 vaccinated participants, it will be necessary to obtain informed consent from 700 participants, assuming that 85% of women actually get inoculated after receiving explanations of the vaccine and agreeing to be inoculated. Additionally, to enroll approximately 2200 unvaccinated participants, 2100 women who do not consent for vaccination will be included in the group in addition to the 15% of women mentioned above who will not actually get inoculated. Therefore, the sample size will be approximately 2800 women who are negative for intraepithelial lesions or malignancy.

## Discussion

Previous studies have confirmed the prophylactic effect of HPV vaccination on cervical cancer in females aged 9–26 years. The FUTURE study showed that the quadrivalent HPV6/11/16/18 vaccine reduced the incidences of HPV16- and HPV18-related cervical precancers and cervical cancer in women aged 16–26 years [10]. The study, which investigated the cost-effectiveness of the vaccine worldwide, recommended the first target age for vaccination to be 9–14 years and the next target age to be up to 26 years [10]. There have been only two large studies on the effects of HPV vaccination in adult women. One of the two was the VIVIANE study using the AS04-HPV-16/18 vaccine, which indicated that the vaccine is approximately 80% effective against persistent infection in adult women [5]. The other study was a randomized controlled trial that demonstrated the efficacy of the quadrivalent HPV6/11/16/18 vaccine in reducing the rate of persistent infections among adult women [9]. Therefore, generating new evidence about HPV vaccination in the young adult population will be worthwhile, particularly in the postlaunch real-world setting.

As mentioned above, adult women are not covered under the national immunization program of Japan due to cost-effectiveness concerns related to high HPV16/18 prevalence. In this study, we will enroll only women with normal cytology results because our previous study (FCCS study) revealed that women from Fukui Prefecture with normal cytology results were basically negative for HPV16/18 [7].

As the Japanese cervical cancer screening program uses only cytology without HPV-DNA testing, there are no available data on the detection of HPV16/18 DNA. However, the FCCS study has shown that the HPV16/18 infection rates were significantly lower among those with normal cytology results than among those with abnormal cytology results (1.0% vs. 22.0%). Therefore, the present study will target women with normal cytology results [7].

While young adult women aged 27–45 years are not covered under the national immunization program, they have the chance to visit gynecologists periodically to undergo cervical cancer screening provided through the national program. This regular visit is a suitable opportunity for vaccine recommendation, as normal cytology results still indicate susceptibility to HPV infection, and during the visit, the necessity of vaccination can be conveyed by the physician directly to the patient, not to her parents or guardians.

A possible limitation of the study is that the study design involves a nonrandomized, and not randomized, intervention. If the study were to adopt a randomized intervention design, we speculate that the participation of the patients cannot be assured under current circumstances in Japan, where the MHLW has suspended its strong recommendation for HPV vaccination.

The findings of this trial might provide robust local evidence supporting HPV vaccination among young adult women aged 27–45 years who show negative cytology results. By utilizing the data from this study, we intend to develop a platform covering both cervical cancer screening and HPV vaccine recommendations for those proven to have negative cytology results. This new platform might serve as an effective means to drive HPV vaccination among those not covered under the national immunization program of Japan and raise questions about the rigid state of the 5-year national immunization program. This study could provide local supportive evidence for preventing HPV infection through HPV vaccination in young adult women and thus contribute to public health improvement in Japan, where active recommendation of HPV vaccination has been suspended by the MHLW for a long time.

